### Study Plan

Patients with TBI are routinely screened on the seventh day after injury. If cognitive dysfunction is detected, the patient may be eligible to participate according to the inclusion and exclusion criteria. Eligible patients will be informed about the study and provided with an information leaflet. If the patient is willing to participate, an appointment will be scheduled.

#### Visit 1

At the initial visit, which will be the seventh day after injury, written informed consent will be confirmed, and the participant will then be allocated to a group. Demographic data and results of neurological examinations will be collected. Neurological function, cognitive function (via scales, MEG, and serum biomarkers), mental behavior, activity of daily living, and quality of life will be assessed. Afterward, the participant will receive a median nerve stimulator and will receive brief training and instructions. Then the stimulation phase for 2 weeks starts. The treatment will be performed in the hospital under the supervision of trained study staff. The participant is advised to contact the principal investigator during interventions if any side effects occur.

#### Visit 2 (1 Month After Injury)

At the second visit, feasibility and safety outcomes will be assessed. Participants will complete the study-specific acceptability questionnaire, and all AEs will be recorded. The stimulation statistics will be downloaded from the app, and the stimulator will be returned to the investigator. Neurological function, cognitive function, mental behavior, activity of daily living, and quality of life will be assessed again.

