Stimulation will be administered for 8 hours per day throughout the 2-week intervention period by trained study personnel. If mild skin irritation or discomfort occurs, the electrodes may be repositioned, and the stimulation intensity reduced while maintaining visible thumb flexion. Stimulation will be suspended if symptoms persist and permanently discontinued if a serious device-related adverse event (AE) or clinically significant intolerance occurs, as determined by the study investigator.

Treatment adherence will be monitored by study personnel and recorded in the CRF, including the daily stimulation duration, any interruptions, device-related problems, and AEs. Device function and electrode contact will be checked before each treatment session. If device malfunction occurs, stimulation will be stopped immediately, the malfunction will be documented, and the device will be inspected or replaced before treatment is resumed. If stimulation is interrupted because of medical procedures, clinical instability, technical problems, or other unavoidable circumstances, participants will resume stimulation as soon as clinically feasible on the same day to complete the planned 8-hour daily treatment whenever possible. Missed stimulation time will not be carried forward to subsequent days. All interruptions and their reasons will be documented and incorporated into the assessment of treatment adherence.

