### Outcomes

#### Primary Outcome

##### Feasibility

Referring to the previous recommendations, the feasibility of this pilot study will be evaluated based on the following measures: (1) enrollment rate—the proportion of participants who meet the eligibility criteria and provide consent after baseline screening; (2) recruitment rate—the mean number of participants enrolled in the study per month; (3) adherence rate—the proportion of completed scheduled stimulation hours, which will be used to assess the acceptability of the interventions; and (4) retention rate—the proportion of participants who complete all outcome measurements from the baseline to follow-up assessments [15,18]. These measures will determine whether to proceed with a future main trial.

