### Exploratory Outcomes

The schedule of enrollment, interventions, and assessments is summarized in Table 1 in accordance with the SPIRIT (Standard Protocol Items: Recommendations for Interventional Trials) guidelines [19]. The main exploratory cognitive outcome will be the change in MMSE score from baseline (visit 1) to 1 month after injury (visit 2). MMSE assessments will be conducted by 2 trained occupational therapists who are blinded to treatment allocation and are not involved in the intervention delivery. Secondary exploratory outcomes will include other cognitive assessments, including Montreal Cognitive Assessment, Verbal Fluency test, Boston Naming Test, Rey-Osterrieth Complex Figure Test, Rey Auditory Verbal Learning Test, Stroop test, Trail Making Test (parts A and B), Symbol Digit Modalities Test, and Digit Span Test [20,21]. Moreover, assessment of mental behavior will be assessed using the Neuropsychiatric Inventory, Pittsburgh Sleep Quality Index, Hamilton Anxiety Scale, Hamilton Depression Scale, Revised Apathy Rating Scale, and Cohen-Mansfield Agitation Inventory [22-26]. Neurological functions will be assessed by the Glasgow Coma Scale and modified Rankin Scale [27,28]. For assessment of activity of daily living and quality of life, the modified Barthel Index, Short Form 36 Health Survey, and Functional Activities Questionnaire will be evaluated. For neuroradiological assessment, functional connectivity within the default mode network and execution control network will be evaluated using MEG. Serum cognitive biomarkers including tau, amyloid beta, glial fibrillary acidic protein, S100 calcium-binding protein B, and alpha-synuclein will be tested.

**Table 1. T1:** Schedule of enrollment, interventions, and assessments.

Time points	Enrollment	Allocation (day 7)	1 month	3 months
Enrollment				
Eligibility screen	✓			
Informed consent		✓		
Randomization		✓		
Interventions				
MNS^a^		2 weeks  ^b^		
Sham MNS		2 weeks 		
Assessments				
Demographics, medical history	✓			
Laboratory data	✓		✓	✓
Neurological examination	✓		✓	✓
Neuroimaging (MRI^c^ and MEG^d^)		✓	✓	✓
Serum biomarkers		✓	✓	✓
Cognitive function		✓	✓	✓
Neuropsychiatric behavior		✓	✓	✓
ADL^e^ and quality of life		✓	✓	✓
Compliance			✓	✓
Drug combination	✓	✓	✓	✓
SAEs^f^ or AE^g^s			✓	✓

a MNS: median nerve stimulation.

b The intervention commenced 7 days after injury and was administered for 2 consecutive weeks.

c MRI: magnetic resonance imaging.

d MEG: magnetoencephalography.

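### The stimulator is returned only at the 1-month visit although staff-delivered in-hospital treatment ends after 2 weeks, leaving about 7 to 11 days with no stated control on its use before the main exploratory MMSE assessment

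*Protocol article*

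**What the plan says.** Two descriptions of how the device is handled stand side by side in the protocol article.

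**Staff-delivered treatment.** The Interventions section says: "Stimulation will be administered for 8 hours per day throughout the 2-week intervention period by trained study personnel". Visit 1 under Study Plan agrees: "The treatment will be performed in the hospital under the supervision of trained study staff". A footnote to the schedule of assessments (Table 1) fixes the timing: "The intervention commenced 7 days after injury and was administered for 2 consecutive weeks". Adherence is a staff record: "Treatment adherence will be monitored by study personnel and recorded in the CRF, including the daily stimulation duration, any interruptions, device-related problems, and AEs".

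**Participant-held device.** Visit 1 also says: "Afterward, the participant will receive a median nerve stimulator and will receive brief training and instructions". Visit 2, one month after injury, closes the loop: "The stimulation statistics will be downloaded from the app, and the stimulator will be returned to the investigator".

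Four other statements bear on the point:
- Interventions: the sham device is set to 0 mA, and participants are told not to change the stimulation settings themselves.
- Blinding: participants are not blinded.
- Exploratory Outcomes: the main cognitive outcome is the change in MMSE from Visit 1 to Visit 2.
- Data Analysis: the MMSE effect size is to inform the sample size of the definitive trial.

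**The concern.** If staff give every session in hospital, there is no evident reason for the participant to be trained on the device, or for the device and its log to come back more than a week after the last session. As written, the device can remain with the participant from the end of treatment to Visit 2. The only stated restriction on participants concerns the settings. It does not address use after the 2 weeks.

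The gap falls just before the main exploratory outcome, and its effect would be one-sided. A sham participant who used the device would receive nothing; an active-arm participant would receive real stimulation. Downloading the log at Visit 2 could show that this had happened but could not undo it. The MMSE difference would then describe 2 weeks of supervised stimulation plus an unknown amount of later use. That is a poor basis for sizing a trial of the 2-week treatment.

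A lesser matter is that stimulation time has two sources, the CRF and the app, and they may cover different periods. The article does not say what the app log is for.

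**Working it through.** The article gives no figure for this point, so there is none to reproduce. The check is arithmetic on the stated schedule.

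**Inputs from the article**
- Treatment starts 7 days after injury and lasts 2 weeks (Table 1 footnote).
- Planned stimulation is 8 h per day (Interventions).
- The device is returned and the log downloaded at 1 month after injury (Visit 2).
- The adherence threshold for progression is 80% (Progression Criteria).

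**Assumptions**
- No visit window is given, so 1 month is taken as day 28 to 31.
- The last treatment day is day 20 if the first session is on day 7, or day 21 if it is the day after.

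**Step 1: planned exposure.** 14 days × 8 h = 112 h.

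**Step 2: length of the gap.** Gap = day of Visit 2 − last treatment day.

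| Visit 2 | Last treatment day 20 | Last treatment day 21 |
|---|---|---|
| Day 28 | 8 days | 7 days |
| Day 30 | 10 days | 9 days |
| Day 31 | 11 days | 10 days |

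The range is 7 to 11 days.

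**Step 3: upper bound on unplanned use.** At an assumed 8 h on every day of the gap:
- shortest gap: 7 × 8 = 56 h, and 56/112 = 50% of the planned hours;
- longest gap: 11 × 8 = 88 h, and 88/112 = 79%;
- 9-day gap: 9 × 8 = 72 h, and 72/112 = 64%.

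These are ceilings. The article gives no rate of use after treatment, and the lower bound is zero.

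**Step 4: does the gap affect adherence?** The Feasibility section defines the adherence rate as "the proportion of completed scheduled stimulation hours, which will be used to assess the acceptability of the interventions". Only the 2 weeks are scheduled, and the Interventions section adds: "Missed stimulation time will not be carried forward to subsequent days". On that definition, hours after the last session add 0 h to the numerator.

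Adherence could rise only if total app hours were used instead. In that case 80% is 0.80 × 112 = 89.6 h. A participant at 60% within the 2 weeks has 0.60 × 112 = 67.2 h and would need 89.6 − 67.2 = 22.4 h of later use, or 22.4/8 = 2.8 days. Nothing in the article says that total app hours will be used.

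**The case against.** The strongest reply has four parts.

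1. **Adherence is protected by its definition.** Staff record it daily in the CRF, it counts scheduled hours, and missed time may not be made up on later days. This stands. A reader might infer that hours logged after treatment could lift a participant over the 80% progression threshold. The article does not support that, because it nowhere makes the app log the adherence measure. The 22.4 h example applies only if the stated definition is set aside.

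2. **Custody is inferred.** Receiving a stimulator may mean only being assigned and fitted with one, and the Visit 2 sentence does not say who held the device until then. Use after treatment is neither described nor permitted. This stands in part. Issue with training at Visit 1 and return at Visit 2 read most naturally as custody by the participant, and no other arrangement is stated. But it would be wrong to say that participants will use the device in the gap, and a full 8 h a day of self-applied stimulation by patients with cognitive dysfunction is an extreme case.

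3. **Two data sources are ordinary, and device accounting belongs in the full protocol.** This stands as far as the order of precedence between CRF and app is concerned. It does not answer the return time, which the article states and which fits poorly with its own account of delivery.

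4. **The MMSE is exploratory, unpowered and does not decide progression.** True, and it limits the severity. The MMSE effect size is nevertheless to inform the next trial's sample size, so what it measures still matters.

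**Conclusion.** The point holds in a limited form. The article's account of staff-delivered, in-hospital treatment over 2 weeks does not fit its account of a device issued to the participant and returned at 1 month. As written, a working device can stay with an unblinded participant for about 7 to 11 days before the main exploratory MMSE assessment, with no stated collection or lock. Any use in that time would add stimulation in the active arm alone.

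The length of the gap rests on 1 month being day 28 to 31 and on treatment ending on day 20 or 21. The effect on the MMSE estimate cannot be sized, because no rate of use is given; 56 to 88 h is a ceiling on exposure, not an expectation. The adherence criterion is unaffected under its stated definition. This is a minor point, worth correcting because it costs almost nothing.

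**What to change.** Three changes of wording:

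1. In Interventions and Visit 1, reconcile who holds and operates the device during the 2 weeks, and say what the participant's training is for if staff deliver every session.
2. Move device collection and the log download from Visit 2 to the last scheduled treatment session, or to the point of early stop.
3. State that any app log used for adherence is limited to the scheduled 2-week period and serves as a cross-check of the CRF record.

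The cost is a protocol clarification. Staff are already present at the last session, so no visit is added. The Results section says that recruitment had not begun at submission, so the change can be in place before the first participant if it is made now.

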#### Visit 3 (3 Months After Injury)

The last visit will be 3 months after injury. In this follow-up phase, the persistence of the MNS effect will be evaluated to determine whether it is sustained or diminishes over time. At the last visit, neurological function, cognitive function, mental behavior, activity of daily living, and quality of life will be assessed for the third time, and the safety data will also be evaluated again.

### Data Protection

All data will be recorded pseudonymously, and the link between number and patient name will be stored on a separate secure clinical network server. The electronically recorded data of this study will be maintained on a password-protected database under the control of the principal investigator. All questionnaires and consent forms will be stored in a locked cabinet in a locked room requiring key card access. All additional information will be stored without any identification of group assignment on a separate database.

### Outcomes

#### Primary Outcome

##### Feasibility

Referring to the previous recommendations, the feasibility of this pilot study will be evaluated based on the following measures: (1) enrollment rate—the proportion of participants who meet the eligibility criteria and provide consent after baseline screening; (2) recruitment rate—the mean number of participants enrolled in the study per month; (3) adherence rate—the proportion of completed scheduled stimulation hours, which will be used to assess the acceptability of the interventions; and (4) retention rate—the proportion of participants who complete all outcome measurements from the baseline to follow-up assessments [15,18]. These measures will determine whether to proceed with a future main trial.

##### Safety Evaluation

Safety will be evaluated throughout the intervention period by recording all AEs, including pain, uncomfortable cutaneous sensation, dizziness, abnormal blood pressure, abnormal heart rhythm, headache, nausea, and seizures. At the completion of the intervention, participants will complete a study-specific 10-item questionnaire based on a 5-point Likert scale (Multimedia Appendix 1) to evaluate treatment acceptability and participant-reported symptoms. The questionnaire evaluates participants’ understanding of the intervention, perceived benefit, treatment comfort, willingness to receive MNS again, and potential treatment-related symptoms. Each item is scored from 1 to 5, with higher scores indicating greater agreement or symptom severity, as appropriate.

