**Methods:**

This study is designed as a prospective, single-center, assessor-blinded, sham-controlled, randomized pilot study. Thirty adult patients with cognitive dysfunction after TBI will be enrolled and randomized to either the stimulation or sham group in a 1:1 allocation ratio. In the stimulation group, MNS is performed on the right wrist (40 Hz, pulse width 300 µs, 20 s on/40 s off, 8 hours per day). The sham group will receive stimulation using an identical device set to deliver 0 mA. Feasibility, safety, and preliminary efficacy will be evaluated at 1 and 3 months after the injury. Feasibility and acceptability will be assessed via recruitment, adherence, retention, and participant-reported acceptability using Likert scales. These measures will be summarized descriptively, and completion rates will be calculated and reported. Safety will be primarily assessed by ascertainment of adverse events from enrollment to 3 months. Further safety assessment will examine side effects using a Likert questionnaire and the impact on peripheral hemodynamic responses. Additionally, the potential efficacy of MNS on cognitive dysfunction will be assessed using multiple cognitive scales; neuroradiological tests, including magnetic resonance imaging and magnetoencephalography; and cognitive-related serum biomarkers.

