### Data Analysis

The feasibility outcomes will be reported using descriptive statistics. Recruitment, enrollment, adherence, and retention rates will be presented with 95% CIs. AEs and their frequency will also be summarized descriptively. Participant-reported symptom and acceptability questionnaire scores will be summarized using frequencies, percentages, medians, and IQRs, as appropriate. Baseline demographic and clinical characteristics will be summarized descriptively by the treatment group. No formal statistical significance testing will be performed for baseline characteristics. Exploratory cognitive outcomes will be analyzed according to the intention-to-treat principle where applicable. Missing outcome data will be handled using multiple imputation if appropriate. As this is a pilot feasibility trial with a small sample size, efficacy analyses are exploratory and are not powered to demonstrate definitive treatment effects. Group differences will be estimated using appropriate statistical methods according to the data distribution, with emphasis placed on effect sizes and 95% CIs rather than statistical significance. No formal adjustment for multiple comparisons will be performed. The estimated effect size for the MMSE will be used to inform the sample size calculation for the future definitive RCT.

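### Participant-reported symptoms, part of a primary safety outcome, have no pre-stimulation reference, which weakens the interpretation of the symptom and AE tables

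*Protocol article*

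**What the plan says.** The Outcomes section places Safety Evaluation under the primary outcome. It lists the events to be recorded: "Safety will be evaluated throughout the intervention period by recording all AEs, including pain, uncomfortable cutaneous sensation, dizziness, abnormal blood pressure", followed by "abnormal heart rhythm, headache, nausea, and seizures". For the participant-reported part it states: "At the completion of the intervention, participants will complete a study-specific 10-item questionnaire based on a 5-point Likert scale". On scoring it says: "Each item is scored from 1 to 5, with higher scores indicating greater agreement or symptom severity, as appropriate". The Visit 2 paragraph places the acceptability questionnaire at 1 month. On either reading it is completed after stimulation has ended.

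Table 1 ticks the SAE/AE row at 1 month and 3 months only. Its footnote fixes the start of treatment: "The intervention commenced 7 days after injury and was administered for 2 consecutive weeks". The visit 1 battery is described as follows: "Neurological function, cognitive function (via scales, MEG, and serum biomarkers), mental behavior, activity of daily living, and quality of life will be assessed". No dizziness, headache or nausea measure is named there.

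The Data Analysis section says: "Participant-reported symptom and acceptability questionnaire scores will be summarized using frequencies, percentages, medians, and IQRs". AEs and their frequency are also summarised descriptively. Neither statement refers to a baseline.

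Other sections describe AE capture more broadly. The Abstract says: "Safety will be primarily assessed by ascertainment of adverse events from enrollment to 3 months". Safety Monitoring has AEs assessed at each intervention session and each follow-up visit, with the principal investigator judging relationship to the intervention.

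**The concern.** Every participant begins stimulation one week after a brain injury with a Glasgow Coma Scale score of 9 to 12 at admission. Some of the listed events, such as dizziness, headache and nausea, can plausibly come from the injury itself. That is general clinical knowledge; the protocol neither states it nor gives a prevalence.

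A severity score taken once, after treatment, is the same whether the symptom was present at day 7 and has eased or has newly appeared. The main exploratory cognitive outcome, by contrast, is defined as change from visit 1. The participant-reported part of a primary outcome has no such reference point.

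Three things are at stake:
- The size of any between-arm difference in symptoms.
- The reader's ability to see whether such a difference was already there before stimulation.
- The basis for the investigator's relatedness judgement, which has no scheduled baseline symptom record to draw on.

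**Working it through.** The protocol states no safety figure, so there is nothing to reproduce. The calculations below only illustrate size.

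**Inputs from the protocol.** 30 participants, 15 per group, 1:1 allocation, no stratification (Sample Size; Randomization).

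**Assumed inputs.** Day-7 prevalence p of a given symptom, 0.2 to 0.6. For steps 2 and 3, persistence s = 0.7 among those who have the symptom, and new-symptom rates among those free of it of q0 = 0.10 (sham) and q1 = 0.30 (active).

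**Step 1: chance imbalance at day 7.** Let X and Y be independent Binomial(15, p) counts in the two arms. P(|X − Y| ≥ k) is the sum of P(X = i)·P(Y = j) over all i, j with |i − j| ≥ k.

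| p | gap ≥ 3 | gap ≥ 4 | gap ≥ 5 |
|---|---|---|---|
| 0.2 | 0.249 | 0.107 | 0.038 |
| 0.3 | 0.318 | 0.161 | 0.071 |
| 0.4 | 0.351 | 0.191 | 0.092 |
| 0.5 | 0.362 | 0.200 | 0.099 |
| 0.6 | 0.351 | 0.191 | 0.092 |

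A gap of 3 is 3/15 = 20 percentage points. These figures are for one symptom. Combining several would need their correlation, which the documents do not give.

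**Step 2: how much of that gap reaches later counts.** With no treatment effect (new-symptom rate q in both arms), a day-7 gap of g patients gives an expected later gap of g × (s − q). For g = 3, s = 0.7 and q = 0.10, this is 3 × 0.6 = 1.8 patients, or 1.8/15 = 12 points. With full persistence (s = 1) it is 3 × 0.9 = 2.7 patients, or 18 points. Lower persistence gives less.

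**Step 3: dilution of a true effect.** The expected post-treatment proportion in an arm is p·s + (1 − p)·q. The between-arm difference is therefore (1 − p)(q1 − q0), whatever the value of s.

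| p | sham | active | difference |
|---|---|---|---|
| 0.0 | 0.10 | 0.30 | 0.20 |
| 0.2 | 0.22 | 0.38 | 0.16 |
| 0.4 | 0.34 | 0.46 | 0.12 |
| 0.6 | 0.46 | 0.54 | 0.08 |

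A true 20-point excess of new symptoms appears as 16, 12 or 8 points when only post-treatment status is counted. This assumes that stimulation adds new symptoms but does not change how long old ones last.

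**The case against.** The strongest counter-argument is the design itself. A concurrent randomised sham arm shares the injury background, so carried-over symptoms balance on average. A reader might infer that pre-existing symptoms count systematically against active stimulation, or that the comparison cannot separate stimulation from injury at all. The documents support neither. What remains is dilution and chance imbalance.

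Several further points stand:
- AE capture is wider than the Table 1 ticks, as Safety Monitoring and the Abstract show. An AE row without a day-7 tick is not odd in itself, and the Compliance row has the same pattern. The gap lies in the missing symptom reference, not in the AE row alone.
- Most questionnaire topics (understanding, perceived benefit, comfort, willingness to repeat) cannot be asked before treatment. The symptom items are described as potentially treatment-related, and their wording is in an appendix not shown. They may already ask about onset, and no particular symptom can be assumed to be an item.
- A definition of an AE as new or worsened may sit in the full protocol, so its absence from the article is not held against the plan.
- The step 1 probabilities are largely ordinary binomial noise at 15 per arm. A baseline record does not remove it; it shows how much was present before treatment.

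The relatedness judgement helps only in part. It applies to reported AEs rather than questionnaire scores, and no scheduled day-7 symptom record informs it. Recall is a weak substitute in unblinded participants enrolled with a Mini-Mental State Examination score of 26 or below.

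**Conclusion.** The point holds in a limited form. The article fixes the symptom questionnaire after treatment, schedules no symptom record before stimulation, and plans post-treatment summaries only. Part of a primary outcome is therefore harder to interpret than it needs to be.

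Under an assumed prevalence of 20-60%, a day-7 gap of 3 or more patients on one symptom has probability about 25-36%, and how far it carries forward depends on persistence. Under the further assumptions shown, a true 20-point excess of new symptoms would appear as 8 to 16 points. All these sizes rest on assumed rates.

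A reader might also infer that the decision to proceed is at risk. The stated safety progression criterion counts only unexpected serious device-related AEs attributable to the intervention, so symptom frequencies do not enter it. This is an interpretability issue worth correcting before recruitment starts, because a day-7 symptom record cannot be recovered after enrolment. It is not a fatal flaw.

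**What to change.** 1. Safety Evaluation and Visit 1: give the symptom items of the questionnaire, and not the acceptability items, at visit 1 before allocation is released. The Randomization section already places release of the code after the baseline assessment.
2. Table 1: add the corresponding tick at day 7.
3. Data Analysis: report symptom scores by arm alongside their day-7 values or as change from day 7. Tabulate AEs by arm as new or worsened since the start of stimulation.

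The cost is a few items at a visit that already carries a full test battery, so a slightly longer baseline visit, plus the protocol wording. The relatedness judgement would then have a scheduled record to refer to.
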